## Abstract

**Background:**

More than half of the world’s population will be overweight or obese by 2035, and it is known that physical exercise, such as high-intensity interval training (HIIT), is a tool for controlling obesity by improving body composition and the metabolic profile. Noninvasive techniques such as therapeutic ultrasound (TUS) and the Aussie current have shown potential in controlling adipose tissue, but their effects combined with HIIT remain unknown. TUS may be combined with the Aussie current to potentiate the specific effects of each intervention, such as lipolysis induced by TUS and lymphatic activation promoted by the Aussie current. The integration of HIIT into this protocol is justified by its ability to stimulate β-oxidation and facilitate the metabolic use of fatty acids mobilized by the electrophysical resources. Furthermore, the use of HIIT as opposed to moderate-intensity continuous training contributes to reducing the total duration of the intervention.

**Objective:**

This study aims to evaluate the effects of TUS+Aussie current combined with HIIT on body composition, serum metabolic profile, and cardiovascular autonomic modulation (CAM) in individuals with overweight and obesity.

**Methods:**

This is a randomized, double-blind (researcher and outcome assessor) clinical study. The participants will be randomized into 3 groups: active TUS+Aussie current with HIIT group, placebo for TUS+Aussie current with HIIT group, and TUS+Aussie current–only group. All participants will undergo nutritional monitoring 30 days before the proposed interventions to adjust macronutrients, optimize energy intake, and improve diet quality. Primary outcomes include changes in subcutaneous adipose tissue thickness, body composition, and serum metabolic profile. Secondary outcomes assess perceived stress, body image, blood biochemistry, sleep quality, and CAM. Data analysis involves linear mixed models estimated using the maximum likelihood method with an appropriate covariance matrix structure.

**Results:**

A total of 60 participants will be recruited and randomized between February 2024 and June 2025. The baseline assessments and intervention are scheduled to be completed in August 2025, and data collection will be completed by the end of September 2025. Data acquisition is still ongoing; therefore, data analysis has not yet been carried out.

**Conclusions:**

This is the first study to combine TUS+Aussie current with HIIT, potentially integrating the effects of lipolysis and fat oxidation and possible changes in the serum metabolic profile and CAM. The results could optimize treatment duration, promote changes in lipid profile, and maintain cardiovascular health in people with overweight and obesity.

**Trial Registration:**

Brazilian Registry of Clinical Trials RBR-4xh6232, Universal Trial Number: U1111-1287-2345; https://ensaiosclinicos.gov.br/rg/RBR-4xh6232

**International Registered Report Identifier (IRRID):**

DERR1-10.2196/71829

## Introduction

### Background

According to a report by the World Obesity Federation, more than half of the world’s population will be overweight or obese by 2035 [1]. Excess abdominal fat is a primary determinant for developing insulin resistance and other metabolic disorders [2]. Lifestyle modification is the most recommended approach for treating and preventing obesity at any stage of life [2]. In addition to exercise and a controlled diet, noninvasive techniques have emerged as safe and effective tools for managing adipose tissue [3,4]. These techniques include different electrophysical agents, such as low-intensity laser [5], cryotherapy [6], radiofrequency [7], infrared radiation [8], and therapeutic ultrasound (TUS) [4,9].

TUS is a therapeutic modality widely used in physiotherapy clinical practice [10,11]. The nonlinear propagation of TUS waves induces mechanical forces on particles at the applied site, resulting in biological effects [4], including pyroptosis [12]. This term refers to a form of programmed cell death mediated by caspase-1 or caspase-11, characterized by the secretion of proinflammatory cytokines [12,13]. Cells undergoing pyroptosis exhibit mitochondrial membrane potential loss; DNA fragmentation; nuclear condensation; and the release of cytoplasmic contents into the bloodstream, including fatty acids [13,14].

TUS can be combined with Aussie electrical current to stimulate the lymphatic system, producing a strong but comfortable paresthesia [11,15]. The Aussie current is characterized by a medium-frequency alternating wave modulated at a low frequency (LF) and is indicated for various applications, including muscle strengthening, pain control, lymphatic drainage, and edema control [11]. The combined effects of these electrophysical resources—TUS and Aussie current—alongside aerobic exercise after therapy may enhance fat β-oxidation. However, despite promising results for cellulite reduction with the combination of TUS and Aussie current [16-18], previous studies are limited by small sample sizes; lack of a placebo group; and insufficient focus on posttherapy clinical outcomes, such as serum metabolic changes [18]. In addition, other forms of intervention have been widely suggested for reducing body composition and promoting significant metabolic changes in individuals with obesity, such as high-intensity interval training (HIIT). HIIT alternates between periods of high intensity and active recovery and has become a popular training method due to its time efficiency.

Although previous studies [19,20] have shown better effects of HIIT on the aerobic capacity of patients with cardiovascular disease when compared to continuous moderate-intensity training, the effects of HIIT on cardiovascular autonomic modulation (CAM) in people with obesity are poorly understood. A systematic review evaluated the effects of HIIT on CAM based on 6 studies that used heart rate (HR) variability as a measure [21]. The results showed that HIIT can improve autonomic modulation by increasing parasympathetic cardiac modulation and reducing sympathetic cardiac modulation in healthy individuals and patients with metabolic syndrome, making it a promising strategy for cardiovascular rehabilitation [21].

As for the effects of HIIT on body composition, another review analyzed body fat percentage, fat mass, and fat-free mass in cycling, running on the ground, and running on a treadmill [22]. The findings showed that all forms of HIIT significantly reduced fat mass (−1.86 kg) and body fat percentage (−1.53%) compared to the control group [22].

Although previous studies have reported reductions in abdominal circumference and body composition following TUS and Aussie current application [3,4,10,11], none have evaluated this technique in combination with HIIT in participants with overweight or obesity. In addition to optimizing time, the combination of both interventions also aims to optimize the breakdown, drainage, and oxidation of fat, promoting weight loss. There is a need for clinical trials to investigate the potential clinical effects of this therapeutic modality in humans, as suggested by animal models [16-18]. Furthermore, this study addresses a relevant public health problem [1]—the increasing prevalence of obesity in young adults—by proposing a multimodal, noninvasive intervention aimed at reducing abdominal adiposity and improving metabolic health, a scope that has been explored little in previous clinical protocols [4,9,11]. The results of this study will determine whether TUS and Aussie current therapy induce changes in body composition, manage serum metabolic profile, and improve CAM indexes.

### Objectives

This pragmatic study aims to evaluate the effects of combined therapy (TUS+Aussie current) alone and combined with HIIT on body composition, serum metabolic profile, and CAM in people with overweight and obesity. This study also investigates the impact of these interventions on perceived stress, body image, and sleep quality in people with overweight and obesity.

## Methods

### Study Design

This is a randomized, pragmatic, placebo-controlled, double-blinded, 3-arm (1:1:1) clinical trial. The protocol was developed in accordance with the SPIRIT (Standard Protocol Items: Recommendations for Interventional Trials) guidelines [23].

This research will be conducted at the Federal University of São Carlos (UFSCar) in the Cardiovascular Physical Therapy Laboratory/Physical Exercise Research Center within the Department of Physical Therapy. Participants will be recruited through social media advertisements. An electronic form hosted on Google Forms will be shared via Instagram. Interested participants who meet the basic inclusion criteria will be contacted via WhatsApp to provide additional information about the study and assess their eligibility. Participants who do not respond to the messages will receive up to 3 phone call attempts at different times. If these contact attempts are unsuccessful, the individual will be considered unreachable and ineligible for the study.

### Ethical Considerations

This study adheres to the ethical principles outlined in the Declaration of Helsinki. The research protocol was approved by the Research Ethics Committee of the UFSCar (approval 64624522.8.0000.5504) and was registered in the Brazilian Registry of Clinical Trials on February 8, 2023, and updated on December 2, 2024 (RBR-4xh6232—Universal Trial Number: U1111-1287-2345). Participants will be informed of their right to withdraw from the study at any time without penalty or loss of benefits. In addition, all collected data will be treated with strict confidentiality and used solely for research purposes. This is an academic study and no compensation will be given to participants.

Before any data collection, the outcome assessor obtains written informed consent from participants. Only those who provide consent proceed to the baseline evaluation and randomization.

The data will be collected on paper and stored in folders at the Cardiovascular Physical Therapy Laboratory (Federal University of São Carlos). The data will be entered into Microsoft Excel (Microsoft Corp) by the physiotherapist responsible for the assessments, reassessments, and follow-ups. In addition, all the data will be available on a public research bench.

The database and electronic analyses will be stored on a secure computer server, with personal log-in access authorized by the principal investigator of this study. The principal investigator will have access to the complete dataset (without the allocation groups), and the data and materials in this paper will be available to other researchers on request. Upon completion of the study, all data and documents will be archived by the principal investigator for 5 years at the Physical Therapy Department of the Federal University of São Carlos.

### Eligibility Criteria

The eligibility criteria for this study are outlined in Textbox 1.

Inclusion and exclusion criteria.
**Inclusion criteria**
Men and womenAges of 18 to 40 years at enrollmentClassified as overweight or having grade-I or grade-II obesity according to the fat mass index as measured using dual-energy x-ray absorptiometryHealthy adults without any chronic or acute disease and who started any physical activity in the previous 3 months
**Exclusion criteria**
Current smokers, individuals with chronic alcohol misuse, illicit substance users, or smokers or ex-smokers less than 12 months oldHistory of body mass reduction treatments using drugs or electrophysical agents such as therapeutic ultrasound and electrotherapy in the previous 12 monthsElectrocardiogram abnormalities, including ischemia, overloads, conduction disorders, and serious arrhythmias such as ventricular tachycardiaPresence of any of the following conditions or diagnoses of diseases: neurological, renal, respiratory, cardiac, or musculoskeletal conditions; venous thrombosis; anticoagulant therapy or bleeding disorders; active cancer or cancer treatment in the previous 5 years; conditions or lesions in the abdominal region; diabetes mellitus type 1 or 2; hypothyroidism or hyperthyroidism; and pregnancy in the previous 12 months

### Randomization and Blinding

In this study, the researchers responsible for the evaluations and those analyzing the data will be blinded. To ensure the feasibility of blinding, the blinded research teams will not participate in the interventions, and all information will be coded to prevent the identification of participants and intervention groups. The effectiveness of blinding will be assessed using a questionnaire completed by the evaluators at the end of the final assessment for each data collection block.

After the initial assessments, participants will be stratified (age range, sex, and fat mass index) and randomly assigned to 1 of 3 groups. Participants in group 1 (active TUS+Aussie current with HIIT [AG]) will undergo combined therapy (TUS+Aussie current) along with the HIIT protocol. Participants in group 2 (placebo for TUS+Aussie current with HIIT [PG]) will undergo placebo combined therapy (TUS+Aussie current) with the devices turned off along with the HIIT protocol. Participants in group 3 (TUS+Aussie current–only group [HG]) will receive only the combined therapy (TUS+Aussie current) without the HIIT protocol.

For stratified randomization, participants will be initially grouped into blocks based on similar characteristics, including age range (20-29 years or 30-40 years), sex (male or female), and fat mass index (overweight, grade-I obesity, or grade-II obesity). These characteristics will be chosen to control for potential confounding factors. Within each block, participants will be then randomized into the 3 study groups using Microsoft Excel, ensuring an unbiased allocation process. Block sizes were not fixed, further reducing the risk of allocation predictability. The randomization process will be conducted by a researcher designated exclusively for this task, who will have no contact with the study participants or the researchers involved in data collection. This researcher will also be responsible for generating random alphanumeric codes to ensure the anonymity of each participant’s information.

### Measures

#### Baseline Evaluation

Participants who meet the eligibility criteria will be considered eligible for randomization and will have a baseline evaluation scheduled. To characterize the sample, the initial assessment records information, such as sex, age, anthropometric data, family history, medication use, educational level, occupation, and comorbidities.

#### Study Assessments and Timeline

All study participants will have to attend 2 face-to-face visits: one at baseline (week –1) and one at the final assessment (week 6). In addition, participants will be assessed by a nutritionist and receive nutritional guidance and diet plans (week 0). The treatment will last 5 weeks. A detailed schedule is available in Table 1.

**Table 1 table1:** Study period.

Time point^a^		Study period								
		Enrollment	Allocation	After allocation						Closeout
		Week −4	Week 0	Week 1	Week 2	Week 3	Week 4	Week 5	Week 6	
**Enrollment**										
	Eligibility screening	✓								
	Informed consent	✓								
	Nutritional evaluation	✓								
	Allocation		✓							
**Interventions**										
	AG^b^			✓	✓	✓	✓	✓		
	PG^c^			✓	✓	✓	✓	✓		
	HG^d^			✓	✓	✓	✓	✓		
**Assessments**										
	SAT^e^	✓	✓						✓	
	Body composition	✓	✓						✓	
	Metabolic profile			✓				✓		
	Perimetry	✓	✓						✓	
	Blood test	✓	✓						✓	
	Questionnaires	✓	✓						✓	
	Exercise test		✓							
	24-h food recall			✓	✓	✓	✓	✓		
	CAM^f^	✓	✓	✓				✓	✓	

^a^Timepoint: evaluation time.

^b^AG: active therapeutic ultrasound+Aussie current with high-intensity interval training group.

^c^PG: placebo for therapeutic ultrasound+Aussie current with high-intensity interval training group.

^d^HG: therapeutic ultrasound+Aussie current–only group.

^e^SAT: subcutaneous adipose tissue.

^f^CAM: cardiovascular autonomic modulation.

#### Initial Evaluation

Initial information (lifestyle and inclusion criteria) will be collected online using a screening form link for men and women. Body mass and height measurements will be taken using a calibrated scale. Participants will be advised to be barefoot and wear light clothing. Height is measured with the participant standing and using a stadiometer. A member of the research team ([name]) is responsible for carrying out all study assessments as well as screening and recruiting participants, minimizing bias.

#### Abdominal Subcutaneous Adipose Tissue

Ultrasound will be used as the main end point to assess abdominal subcutaneous adipose tissue (SAT) [4]. Intrarater reliability was assessed in previous studies [24]. A GE HealthCare Venue 40 ultrasound (model NZCART; GE Medical Systems, Ltd) is used. Subcutaneous fat, defined as the distance in centimeters between the dermis and the external surface of the fascia of the abdominal muscles, is measured using a linear transducer with a frequency of 12 MHz placed transversely 1 cm above and 1 cm below the umbilical scar [25,26]. Participants will be examined in the supine position without any artifact compressing the abdominal region, with their knees bent, and instructed to breathe in and out. A total of 3 measurements will be taken, each at the end of an exhalation, with minimal pressure on the abdominal cavity for greater measurement precision [27,28].

#### Body Composition

To determine total body mass, fat mass percentage per region, and visceral fat, we use dual-energy x-ray absorptiometry (DXA; Hologic Discovery A). This assessment is considered the gold standard for evaluating body composition in individuals with overweight and obesity [29]. In addition, DXA is used to classify participants as overweight or obese (grade I and II) [30]. Considering that hormonal variation throughout the menstrual cycle can influence body composition results, especially through fluid retention and water redistribution, all female participants will be assessed during the follicular phase of the menstrual cycle, a phase in which there is greater hormonal stability and a reduction in extracellular fluids, providing greater accuracy in body composition measurements [31].

Participants must fast for 4 hours, refrain from vigorous exercise for at least 12 hours, avoid caffeine and alcohol for the previous 24 hours, and consume a normal meal the night before the test. They should not wear any metal objects or accessories during the test to prevent interference with the total body composition results. The participant is placed in a supine position with internal rotation of the thighs, legs, and feet and instructed not to speak or move during the examination. The results obtained will be transmitted to a computer connected to the equipment, where the report shows the data in grams and percentages and which will be used to analyze total lean mass (kg), total bone mass (percentage), total fat mass (g), fat mass index (kg/m^2^), fat mass in the android and gynoid regions (g), and visceral fat (g) and, through calculations, deduce subcutaneous fat [32,33].

#### Serum Metabolic Profile

Venous blood samples will be collected in the cubital fossa by a specialized professional after the participants have fasted for 3 hours following a standardized meal. Blood samples will be taken 3 times: before and immediately after the TUS+Aussie current session and immediately after HIIT. Each tube of blood collected will be left to stand at room temperature for 30 minutes. They will then be centrifuged at 1450 × g for 10 minutes (Sorvall ST 8 Benchtop Centrifuge; Thermo Scientific). The serum is divided into 3 aliquots in 1.5-mL microtubes using 5-mL disposable pipettes and stored immediately at −80 °C until further analysis. The serum samples will then be thawed at the UFSCar Department of Chemistry and sent for analysis using the hydrogen nuclear magnetic resonance technique. Serum glycerol, total cholesterol, very low–density lipoprotein, low-density lipoprotein (LDL), high-density lipoprotein, and triglycerides will be assessed. These will be measured using wet chemistry (except for LDL, which will be calculated using the Friedwald equation; ADVIA 1800; Siemens). The experimental procedures for this analysis will follow those described in the work by De Favari Signini et al [34] and Castro et al [35].

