#### Biochemical Blood Tests

Participants will be referred to a specialized clinic for blood collection. They will be instructed to fast for 10 hours before the test. The following will be collected: complete blood count, glycated hemoglobin (through high-performance liquid chromatography), fasting glycemia, insulin resistance (through enzymatic and chemiluminescent immunoassay), evaluation of the homeostatic model, C-reactive protein (through immunoturbidimetry), homocysteine (through chemiluminescence), total cholesterol, high-density lipoproteins, and LDLs and triglycerides (through the enzymatic method). The tests will be clinically relevant in the context of obesity and abdominal adiposity and may contribute to future studies to determine whether any changes occur in these variables after the intervention. The results will be reported by the unit’s physician and sent to the researcher.

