### Outcomes

#### Primary Outcomes

The primary outcomes involve a comparison (between groups) of the effect of 10 sessions of combined therapy (TUS+Aussie current) alone versus in combination with HIIT, specifically on abdominal SAT thickness, body composition, metabolic profile, and serum glycerol release.

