## Discussion

### Implications

This is the first study to combine TUS+Aussie current with HIIT, potentially integrating the effects of lipolysis and fat oxidation and possible changes in the serum metabolic profile and CAM. The results could optimize treatment duration, promote changes in lipid profile, and maintain cardiovascular health in people with overweight and obesity. The combined protocol is expected to lead to weight loss in the participants compared to the therapies alone. In addition, it is believed that the population with a higher percentage of fat will benefit more from a reduction in abdominal fat thickness (measured through ultrasound imaging) and body fat mass (measured through DXA) after 10 intervention sessions in the AG. This hypothesis assumes that the combination of TUS+Aussie current will promote lipolysis (breakdown of adipocytes measured through serum glycerol collection) and lymphatic drainage into the bloodstream. In addition, by performing HIIT after applying TUS+Aussie current, serum fatty acids will be β-oxidized during exercise.

Scientific literature lacks studies that evaluate the effects of TUS combined with Aussie current with or without HIIT. A controlled, randomized experimental design will be used that follows the SPIRIT guidelines [23] and describes the parameters used to achieve the best results for the population studied.

To the best of our knowledge [4,9,11,15,18], this study will be the first clinical trial to compare the effects of TUS combined with Aussie current and HIIT in participants with overweight and grade-I or grade-II obesity. The findings will provide evidence regarding the effects or lack thereof of this therapeutic approach. Furthermore, as a randomized clinical trial, it will contribute to systematic reviews, fostering new evidence syntheses and addressing existing knowledge gaps.

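### In the within-session samples, glycerol released by the treatment could be read as triglyceride and lower calculated LDL, unless the triglyceride value is glycerol-blanked or comes from NMR

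*Protocol article*

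**What the plan says.** All references are to the Protocol article.

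- **Samples.** Under Serum Metabolic Profile: "Blood samples will be taken 3 times: before and immediately after the TUS+Aussie current session and immediately after HIIT". Participants have "fasted for 3 hours following a standardized meal". Table 1 places this profile in weeks 1 and 5.
- **Analytes and method.** The same section lists serum glycerol, total cholesterol, VLDL, LDL, "high-density lipoprotein, and triglycerides will be assessed". The next sentence reads: "These will be measured using wet chemistry (except for LDL, which will be calculated using the Friedwald equation; ADVIA 1800; Siemens". The sentence before the list sends the same serum for hydrogen NMR, and Table 2 gives venous collection and NMR, not wet chemistry, as the method for metabolic profile. Procedures are referred to two cited papers.
- **Expected effect.** Under Implications, the hypothesis is that TUS+Aussie current "will promote lipolysis (breakdown of adipocytes measured through serum glycerol collection".
- **Status.** The primary outcomes are "abdominal SAT thickness, body composition, metabolic profile, and serum glycerol release".
- **Analysis.** Under Statistical Methods for Primary and Secondary Outcomes, a linear mixed model has group, moment (before and after the intervention), time (baseline, after TUS+Aussie current, after HIIT) and their interactions as fixed factors.

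**The concern.** Glycerol-based triglyceride assays split triglyceride and measure the glycerol set free. Without a glycerol blank, glycerol already in the serum is reported as triglyceride. This assay principle is general laboratory knowledge and is not stated in the article.

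In routine samples such an offset may be roughly constant and drop out of comparisons. Here the device is meant to change the interfering substance between one sample and the next, and to do so under active but not placebo application. An error of this kind would follow the time and group-by-time effects that the model tests, so it would not cancel.

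Calculated LDL subtracts one fifth of triglycerides (in mg/dL), so the same glycerol would also lower LDL. One release of glycerol could then appear as three findings within the primary metabolic outcomes: higher glycerol, higher triglycerides and lower LDL. The last would look like a benefit.

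**Working it through.** The plan gives no figure to reproduce on this point, and no glycerol values. The check sizes the error under stated assumptions.

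**1. Inputs**

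| Input | Value | Source |
|---|---|---|
| Triglyceride method | Wet chemistry; NMR also named | Serum Metabolic Profile; Table 2 |
| LDL | Friedewald: TC − HDL − TG/5 (mg/dL) | Equation named in Serum Metabolic Profile; formula is standard |
| Evaluable participants per arm | 18 | Sample Size |
| Glycerol difference between the samples or arms compared | 0.05 to 0.4 mmol/L | Assumption |
| Baseline triglycerides | 80 to 180 mg/dL | Assumption |
| SD of within-session change | TG 15, 25, 40 mg/dL; LDL 5, 10, 15 mg/dL | Assumption |
| Conversion | 1 mmol/L TG = 88.57 mg/dL | Unit conversion |

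**2. Size of the error if the assay is unblanked**

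One mole of free glycerol reads as one mole of triglyceride:

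- TG error = 88.57 × glycerol difference
- LDL error = −(TG error)/5

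| Glycerol difference (mmol/L) | TG error (mg/dL) | LDL error (mg/dL) |
|---|---|---|
| 0.05 | +4.4 | −0.9 |
| 0.1 | +8.9 | −1.8 |
| 0.2 | +17.7 | −3.5 |
| 0.3 | +26.6 | −5.3 |
| 0.4 | +35.4 | −7.1 |

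At 0.1 mmol/L the triglyceride error is 8.9/180 = 4.9% to 8.9/80 = 11.1% of baseline. With a blanked assay, or with NMR as the source, both columns are zero.

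**3. Which contrasts are exposed**

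- *Within-session time effects in one arm:* the whole glycerol change between the samples counts.
- *AG versus PG:* both arms do the same HIIT, so glycerol released by exercise largely cancels. Only the device-attributable difference counts.
- *HIIT versus no HIIT (against HG):* any glycerol change caused by HIIT itself would count at the post-HIIT time.
- *Pre-session sample, week 1 to week 5:* each is drawn before that day's device and exercise, so the acute rise largely does not enter.

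**4. Chance that a pure artefact reaches P<.05 between two arms**

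With 18 per arm the standard error of the difference is SD × √(2/18) = SD/3. In the normal approximation, the probability is Φ(error/(SD/3) − 1.96). For triglycerides, 0.1 mmol/L and SD 15: 8.857/5 = 1.771, and Φ(1.771 − 1.96) = 0.425.

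| Outcome, between-arm glycerol difference | Smallest SD | Middle SD | Largest SD |
|---|---|---|---|
| TG, 0.1 mmol/L | 0.425 | 0.185 | 0.098 |
| TG, 0.2 mmol/L | 0.943 | 0.566 | 0.264 |
| LDL, 0.1 mmol/L | 0.185 | 0.077 | 0.054 |
| LDL, 0.2 mmol/L | 0.566 | 0.185 | 0.105 |

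These are for a single unadjusted two-sided 5% test. The planned multiplicity adjustments would lower them.

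**The case against.** The strongest objection is that no interference is shown. The article says only wet chemistry and leaves the procedure to cited papers, and whether a reagent is glycerol-blanked is detail that an article commonly omits. NMR is named for the same serum and is the only analytical method in Table 2 for this outcome; if it supplies the triglyceride value, this interference does not arise. This stands. A reader might infer that the triglyceride and LDL results will be biased, but the documents do not support that.

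Three narrower objections also stand.

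- A reader might apply the full within-session glycerol rise to AG versus PG. Exercise is common to both arms, so that would overstate the error.
- A reader might extend the point to the clinic lipids, since Biochemical Blood Tests names "LDLs and triglycerides (through the enzymatic method". That is a separate panel after a 10-hour fast, scheduled in Table 1 at weeks −4, 0 and 6 and not drawn around a session. It says nothing about how the session samples are assayed, and it is outside this point.
- Subtracting glycerol from a result that is already blanked would itself create a bias.

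What survives does not depend on a missing laboratory detail. The article itself combines wet-chemistry triglycerides, a calculated LDL, and samples timed to capture glycerol release, and it names two methods without saying which one supplies the analysed value. Requiring a blanked value does no harm if the assay is already blanked.

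**Conclusion.** The point holds as a conditional risk confined to the within-session samples. It needs two things that the article leaves unsettled: that wet chemistry supplies the analysed triglyceride value, and that the assay is not glycerol-blanked.

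If both are true, each 0.1 mmol/L difference in free glycerol adds about 8.9 mg/dL to triglycerides and takes about 1.8 mg/dL from calculated LDL, in the within-session time and group-by-time effects. Pre-session changes from week 1 to week 5 are largely unaffected. If either is false, the error is zero.

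The triglyceride artefact could matter with 18 per arm; the LDL artefact is small unless the glycerol difference is large. The glycerol range, baseline triglycerides and SDs are assumptions, so these figures describe what could happen and do not estimate a bias in this trial.

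**What to change.** 1. Reconcile Serum Metabolic Profile with Table 2: state whether NMR or wet chemistry supplies the analysed triglyceride value, and which supplies glycerol.
2. If wet chemistry supplies triglycerides in the session samples, use a glycerol-blanked value.
3. Only if the assay is confirmed unblanked, compute corrected TG = TG − free glycerol, both in mmol/L and from the same serum. Do this before analysing triglycerides and before calculating LDL. Do not subtract from a blanked result.

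**Cost.** No new visit or sample is needed, because glycerol is already among the analytes. The subtraction needs glycerol and triglycerides on compatible molar scales, and the corrected value carries the error of both measurements. According to the Results section, analysis starts only after the last reassessment, so the rule can be written down before any results are seen.
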